## **7.2 Study Population**

The immunogenicity analysis will be based on the intent-to-treat population, which is defined as all subjects who received a study vaccine and had evaluable serum sample after vaccination. All maternal subjects who received any amount of study vaccine will be included in the safety population.

## **7.3 Demographics**

Descriptive statistics for demographic and subject characteristics prior to study vaccination including age, weight, height, gravidity and week of gestation will be reported.

## **7.4 Analysis of Immunogenicity**

The immune response to the three vaccine viral strains is assessed by calculation of the geometric mean titers (GMT) of anti-HA antibodies, geometric means of post- to pre-vaccination antibody titer ratios (GMTR, with 95% confidence intervals), seroprotection rates (percentage of subjects with a titer  $>1:40$  at 4 weeks after vaccination and at the end of gestation period), seroconversion rates. The seroconversion rate is defined as the percent of subjects with a pre-vaccination titer  $< 1:10$  achieving a titer  $\geq 1:40$  or with pre-vaccination titer  $\geq 1:10$  having at least a four-fold rise at 4 weeks after vaccination and at the end of gestation period. As for the rate of seroprotection and seroconversion rate, the 95% exact (Clopper-Pearson) confidence interval will be provided as well.

European Agency for the Evaluation of Medicinal Products/Committee for Proprietary Medicinal Products (CPMP) immunogenicity criteria for licensed influenza vaccines specifies 70% seroprotection or 40% seroconversion, or a GMTR of 2.5 for individuals between 18 and 60 years of age.[12]

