pregnant women revealed no excess malignancies in the fetus. [7] A similar but smaller study revealed no harmful effects of the flu vaccine on the fetus or the mother. [8] More recent research found no serious adverse effects from the flu vaccine in the perinatal period or during the first six months of infant life. [9] Although the numbers of patients in these studies are relatively small, these results are reassuring.

According to the previous result, in the season of 2010-2011, the adults (aged between 20 and 60) had the seroprotection rates (HAI titer  $\geq 1:40$ ) were 92.1% against influenza A/H1N1 virus, 85.7% against influenza A/H3N2 virus and 44.4% against influenza B virus 3 weeks after vaccination. The seroconversion rates were 79.4% against influenza A/H1N1 virus, 68.3% against influenza A/H3N2 virus and 28.6% against influenza B virus.

Moreover, 68.3% were females. Among these 43 female subjects, the seroprotection rates were 90.7% against influenza A/H1N1 virus, 88.4% against influenza A/H3N2 virus and 48.8% against influenza B virus 3 weeks after vaccination. The seroconversion rates were 79.1% against influenza A/H1N1 virus, 76.7% against influenza A/H3N2 virus and 34.9% against influenza B virus. Furthermore, 26 females was aged between 18~40 years old, inclusive. Among these 26 female subjects, the seroprotection rates were 92.3% against influenza A/H1N1 virus, 88.5% against influenza A/H3N2 virus and 52.8% against influenza B virus 3 weeks after vaccination. The HAI titer geometric mean fold rise was  $18.8 \pm 4.9$  against influenza A/H1N1 virus,  $14.2 \pm 5.2$  against influenza A/H3N2 virus and  $5.2 \pm 4.0$  against influenza B virus 3 weeks after vaccination. The seroconversion rates were 84.6% against influenza A/H1N1 virus, 80.8% against influenza A/H3N2 virus and 38.5% against influenza B virus.

Another trial on infants between 6 to 12 months old, 57 subjects were included to receive two vaccinations at 4 weeks apart. The seroprotection rate before vaccination were 8.8% against influenza A/H1N1, 10.5% against influenza A/H3N2 virus and 0.0% against influenza B virus. The mean HAI titer geometric before vaccination were  $6.5 \pm 2.4$  against influenza A/H1N1 virus,  $8.2 \pm 4.6$  against influenza A/H3N2 virus and  $5.2 \pm 1.2$  against influenza B virus.

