### **2.1 Primary Objective**

- To evaluate the immune response of the three vaccine viral strains by calculation of the geometric mean titers (GMT) of anti-HA antibodies, geometric means of post- to pre-vaccination antibody titer ratios, seroprotection rates, and seroconversion rates.

The primary endpoint will be the seroprotection rate which is defined as the proportion of subjects with HAI titer  $\geq 1:40$ . The other immunogenicity endpoints include seroconversion rate and geometric mean folds increase in HAI titer. Immunogenicity profile will be assessed before vaccination, 4 weeks after the vaccination and at the end of gestation period.

Moreover, the HAI titer of the cord blood will also be measured and compared with the maternal blood sample.

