## **5.2 Immunogenicity**

Serum samples will be obtained prior to vaccination, and 4 weeks post-vaccination. Moreover, serum samples of maternal subject at the end of gestation period (delivery) and the cord blood sample will also be obtained, if applicable. Serum samples will be tested for anti-hemagglutinin (HA) antibodies by hemagglutination inhibition (HAI), and assays will be performed at Adimmune Corporation designated central laboratory. Subjects will be considered to be seronegative if subjects' serum HAI titer  $< 1:10$ . The seroconversion is defined as the post-vaccination serum at least 1:40 for whom had negative pre-vaccination or a four-fold or greater increase in HAI titers in subjects who had positive pre-vaccination serum.

All antigens used in this study will be formalin-inactivated whole viruses. The testing

antigens will be provided by the designated laboratory. The standard microtiter method will be used. Antibody titrations will be done in duplicate and the titer assigned to each sample will be the geometric mean of two independent determinations.

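### Seroprotection, the primary endpoint, is a titre of at least 1:40 in Section 2.1 but strictly above 1:40 in Section 7.4

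*Protocol*

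**What the plan says.** Section 2.1 Primary Objective names and defines the primary endpoint: "The primary endpoint will be the seroprotection rate which is defined as the proportion of subjects with HAI titer $\geq 1:40".

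Section 1 Introduction reports the 2010-2011 adult results on that same cut-off: "had the seroprotection rates (HAI titer $\geq 1:40$ ) were 92.1% against influenza A/H1N1 virus".

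Section 7.4 Analysis of Immunogenicity defines the seroprotection rate again, in a parenthesis, as the percentage of subjects with a titre ">1:40$ at 4 weeks after vaccination and at the end of gestation period". In the next sentence it defines seroconversion for women with a pre-vaccination titre below 1:10 as "achieving a titer $\geq 1:40$ or with pre-vaccination titer $\geq 1:10$ having at least a four-fold rise". Section 5.2 gives the same seroconversion rule.

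On how a titre arises, Section 5.2 specifies the standard microtiter method in duplicate: "the titer assigned to each sample will be the geometric mean of two independent determinations".

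For the rates, Section 7.4 adds that "the 95% exact (Clopper-Pearson) confidence interval will be provided as well". It also cites a European criterion that "specifies 70% seroprotection or 40% seroconversion, or a GMTR of 2.5 for individuals between 18 and 60 years of age".

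**The concern.** The two definitions differ only for women at exactly 1:40. If the titre were continuous that would not matter. An HAI titre is read on a dilution series, so 1:40 can be an attainable value with real probability.

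An analyst who programs Section 7.4 literally would report a different quantity from the endpoint declared in Section 2.1, and the difference can go only one way. The result would no longer be comparable with the prior-season rates. It would also disagree with the seroconversion rule in the same paragraph: a woman who goes from below 1:10 to 1:40 would meet the response definition and fail the protection definition. If the mismatch were noticed only after the titres were known, choosing between the two would be a post hoc decision on the primary endpoint.

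**Working it through.** **Step 1: the wording side by side.**

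| Place | Quantity | Rule at 1:40 |
|---|---|---|
| Section 1 | Prior-season seroprotection | counts (at least 1:40) |
| Section 2.1 | Primary endpoint, seroprotection | counts (at least 1:40) |
| Section 5.2 | Seroconversion from seronegative | counts (at least 1:40) |
| Section 7.4 | Seroconversion from seronegative | counts (at least 1:40) |
| Section 7.4 | Seroprotection | does not count (above 1:40) |

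One entry disagrees with the other four. A PDF reading error is unlikely, because the at-least sign at 1:40 and 1:10 survives in the very next sentence of 7.4. The source PDF could not be inspected.

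**Step 2: can a titre of exactly 1:40 occur?** Assumption: a two-fold series through 1:10 and 1:40, which the cut-offs suggest but the protocol does not state. Two readings of 1:40 give √(40 × 40) = 40. The next assigned value is √(40 × 80) = 56.6. The strict rule therefore moves the effective cut-off from 1:40 to about 1:56.6.

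**Step 3: the plan's own power figure.** Section 7.1 states power for seroconversion against 40%, n = 60, 5% two-sided. The exact binomial test rejects at X ≥ 33 or X ≤ 16. Power is above 99.99% at 84.6% and at 80.8%. At 38.5% it is 0.0069 + 0.0376 = 4.46%, as stated. Seroconversion uses at least 1:40 throughout, so these figures do not depend on the disputed symbol.

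**Step 4: effect per woman.** With 60 evaluable women, one woman at exactly 1:40 moves the seroprotection rate by 1/60 = 1.67 points. Illustration from the prior rates in women aged 18-40 (Section 1: 92.3%, 88.5%, 52.8%), rounded to whole women out of 60, with an assumed share at exactly 1:40:

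| Share at 1:40 | H1N1 | H3N2 | B |
|---|---|---|---|
| 0% | 55/60 = 91.7% | 53/60 = 88.3% | 32/60 = 53.3% |
| 5% (3 women) | 86.7% | 83.3% | 48.3% |
| 10% (6) | 81.7% | 78.3% | 43.3% |
| 15% (9) | 76.7% | 73.3% | 38.3% |
| 20% (12) | 71.7% | 68.3% | 33.3% |

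The point estimate reaches 70% (42/60) when 55 − 42 = 13 women (21.7%) sit at 1:40 for H1N1, and 53 − 42 = 11 (18.3%) for H3N2.

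**Step 5: how large might the share be?** Assumptions: log-normal titres, geometric SD 2.5 to 4.5, so σ = log2(2.5) = 1.32 to log2(4.5) = 2.17, and μ = log2(GMT). If both readings always agree, the 1:40 cell covers a full two-fold step:

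P = Φ((log2 80 − μ)/σ) − Φ((log2 40 − μ)/σ).

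If duplicates resolve half-steps, the cell shrinks to:

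P = Φ((log2 56.6 − μ)/σ) − Φ((log2 40 − μ)/σ).

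| GMT | Full step, σ 1.32 / 2.17 | Half step, σ 1.32 / 2.17 | P(titre ≥ 40), σ 1.32 / 2.17 |
|---|---|---|---|
| 40 | 27.5% / 17.8% | 14.7% / 9.1% | 50% / 50% |
| 60 | 29.4% / 18.2% | 14.5% / 9.1% | 67% / 61% |
| 150 | 17.2% / 14.8% | 6.9% / 6.9% | 93% / 81% |
| 200 | 11.9% / 12.9% | 4.5% / 5.8% | 96% / 86% |

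The range is about 9-30% at a GMT of 40-60 and 4-17% at 150-200. The last column shows which strain each range can describe: a GMT of 40-60 fits a strain like B (52.8%), and 150-200 fits strains like H1N1 and H3N2.

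**The case against.** Section 2.1 is the only place that expressly defines the primary endpoint, and three other places agree with its cut-off. The symbol in 7.4 therefore looks like a slip that a careful analyst would resolve correctly. The study is descriptive, the only planned test concerns seroconversion, and the European criterion is met by any one of three measures, two of which this symbol does not touch. All of that stands. It limits the consequence but does not remove the contradiction, and the protocol nowhere says that 2.1 prevails over 7.4, or the reverse.

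Three stronger readings are tempting and are not supported.

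- **A collapse in the chance of meeting 70%.** If success meant a lower 95% Clopper-Pearson bound above 70%, at least 50 of 60 would be needed (lower bound 71.5%; 69.6% at 49). The chance would fall from 92.1% at a true rate of 88.5% to 59.7% at 83.5% and 22.9% at 78.5%. The protocol states no such rule; it provides the interval and cites 70% without saying how it is applied. If 70% is read as a point estimate (at least 42 of 60), the same three probabilities are above 99.9%, 99.7% and 95.6%.
- **Exactly 1:40 as a common result.** The protocol gives no titre distribution. The 30% end of the range needs a GMT near 60, which implies at most 67% seroprotected. That does not fit the 88.5% prior rate for H3N2.
- **Extending the correction to cord blood.** Section 2.1 only has cord-blood titres measured and compared with maternal blood. No cord-blood seroprotection rate is defined, so adding one would be a new endpoint.

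**Conclusion.** The point holds as a wrong threshold in the analysis section for the primary endpoint. Followed literally, Section 7.4 gives a seroprotection rate equal to or below the one declared in Section 2.1, not comparable with the prior-season rates and out of step with the seroconversion rule beside it. This conclusion rests on the wording and on 1:40 being an attainable titre.

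The size is 1.67 points per woman at exactly 1:40 with 60 evaluable, and slightly more if fewer are evaluable. The number of such women cannot be fixed from the protocol. The ranges of 4-17% and 9-30% are conditional on the log-normal, two-fold and duplicate-reading assumptions and on the assumed GMT. Sample size and stated power do not change. Because the primary endpoint itself has two incompatible definitions, it should be corrected even though the practical effect may prove small.

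**What to change.** In Section 7.4, replace the strict inequality in the seroprotection definition with at least 1:40, for the maternal rates at 4 weeks and at the end of gestation, so that it matches Section 2.1. If a statistical analysis plan exists, check that it carries the same rule. Leave cord blood as it is. Make the change before the titres are unblinded, so that the choice cannot depend on the results. The cost is one character in the text; sampling, assays, sample size and power are untouched.

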## **7.5 Analysis of Safety**

The safety end points are the frequency, duration, and intensity of solicited adverse events during the 7 days after each vaccination and the incidence of serious adverse events during the study period.

The Medical Dictionary for Regulatory Activities (MedDRA) Terminology will be used to classify all adverse events with respect to System Organ Class (SOC) and preferred term. In the case of severity and relationship summaries, the most severe event and the most directly related event will be presented in summary tables in the case of multiple occurrences per subject.

## **8. ETHICAL AND LEGAL ASPECTS**

### **8.1 Good Clinical Practice**

The procedures set out in this study protocol, pertaining to the conduct, evaluation, and documentation of this study, are designed to ensure that the sponsor and investigator abide by good clinical practice (GCP). Compliance with these regulations also constitutes compliance with the ethical principles described in the current revision of the Declaration of Helsinki (Seoul, October 2008).

### **8.2 Delegation of Investigator Responsibilities**

Responsibilities of the investigators conducting the trial in addition to those stated before are enumerated below:

- Obtain Institutional Review Board (IRB) approval to conduct the clinical trial.
- Provide sponsor with written documentation that the study protocol, any protocol amendments, and the informed consent form have received IRB approval.
- Provide sponsor with a list of IRB members, including their affiliations and

qualifications. As an alternative, a General Assurance number (as assigned by the Department of Health and Human Services) fulfills this requirement.

- Report to the IRB as required. The IRB must assume continued responsibility for the study and review the research on an annual basis.
- Maintain a file of all communications with the IRB on issues related to the clinical trial.
- Conduct the study according to the protocol, ICH - GCP guidelines and in accordance with the Declaration of Helsinki.

### **8.3 Subject Information and Informed Consent**

Written informed consent must be obtained from all subjects prior to study participation. The informed consent form documents the information the investigator provides to the subject and the subject's agreement to participate. The investigator will fully explain the nature of the study, along with the aims, methods, anticipated benefits, potential hazards, and discomfort that participation might entail. The informed consent must be signed and dated by each subject or legal representative before entering the study and prior to the performance of any study specific procedures.

Investigational site must provide the sponsor (or designee) with a copy of the informed consent approved by that site's Institutional Review Board (IRB), or Ethics Committee (EC). The subject or the subject's legally authorized representative must sign the informed consent form. The original signed consent form will be retained in the subject's study records, and a copy will be provided to the subject. The sponsor will assure that each informed consent meets the basic elements of informed consent.

### **8.4 Confidentiality**

Subject names will not be supplied to the sponsor. Only the subject number and subject initials will be recorded in the case report form, and if the subject name appears on any other document (e.g., laboratory report), it must be obliterated before a copy of the document is supplied to the sponsor. Study findings stored on a computer will be stored in accordance with local data protection laws. The subjects will be told that representatives of the sponsor or IRB may inspect their medical records to verify the information collected, and that all personal information made available for inspection will be handled in strictest confidence and in accordance with local data protection laws.

The investigator will maintain a personal subject identification list (subject numbers with the corresponding subject names) to enable records to be identified.

## **8.5 Protocol Amendments**

The investigator is responsible for properly notifying the sponsor of protocol changes or revisions. The investigator without prior written authorization from the sponsor may make no changes to this protocol.

## **8.6 Approval of the Study Protocol and Amendments**

Before the start of the study, the study protocol, informed consent document, and any other appropriate documents will be submitted to the independent ethics committee (IEC)/institutional review board (IRB) with a cover letter or a form listing the documents submitted, their dates of issue, and the site (or region or area of jurisdiction, as applicable) for which approval is sought. If applicable, the documents will also be submitted to the authorities, in accordance with local legal requirements.

Study medication can only be supplied to the investigator after documentation on all ethical and legal requirements for starting the study has been received by the sponsor. This documentation must also include a list of the members of the IEC/IRB and their occupation and qualifications. If the IEC/IRB will not disclose the names of the committee members, it should be asked to issue a statement confirming that the composition of the committee is in accordance with GCP. The IRB General Assurance Number may be accepted as a substitute for this list. Formal approval by the IEC/IRB should preferably mention the study title, study code, study site (or region or area of jurisdiction, as applicable), and any other documents reviewed. It must mention the date on which the decision was made and must be officially signed by a committee member.

Before the first subject is enrolled in the study, all ethical and legal requirements must be met.

The IEC/IRB and, if applicable, the authorities must be informed of all subsequent protocol amendments, in accordance with local legal requirements. Amendments must be evaluated to determine whether formal approval must be sought and whether the informed consent document should also be revised.

The investigator must keep a record of all communication with the IEC/IRB and, if applicable, between a coordinating investigator and the IEC/IRB. This also applies to any

communication between the investigator (or coordinating investigator, if applicable) and the authorities.

## **9. STUDY MONITORING AND AUDITING**

Monitoring and auditing procedures developed by the sponsor or its designee will be followed, in order to comply with GCP guidelines. On-site checking of the case report forms for completeness and clarity, cross-checking with source documents, and clarification of administrative matters will be performed.

### **9.1 Study Monitoring**

The sponsor designated representative will monitor this study in accordance with the Declaration of Helsinki (Seoul, October 2008). Responsibilities include study monitoring (adherence to protocol, review accuracy and completeness of records, source document checks); evaluation of study data (drug accountability, communication, and written records); monitoring of site facilities to ensure continued adequacy and AE monitoring. The designee will maintain regular contact with each investigational site, through telephone contact and on-site visits, to ensure that the investigational plan and DOH and other national and/or local regulations are followed. These contacts are also to ensure that timely and accurate data are submitted, that problems with inconsistent and incomplete data are addressed, and that the site facilities and management continue to be adequate for this study. Any questions regarding these matters should be addressed to the designee.

The designee will evaluate and summarize the results of each visit in written reports, identifying any repeated data problems with the investigator and specifying recommendations for resolution of noted deficiencies.

### **9.2 Source Documentation, Records Retention, and Availability**

The investigator must maintain detailed, primary records (i.e., source documents) of the data for each subject screened and treated to study treatment. Examples of source documents may include, but are not limited to: signed informed consent forms, office or clinic records, hospital records, progress notes, diagnostic test results, telephone contact reports, laboratory reports, consultant's opinions/findings, referral letters, study drug inventory records.

The investigator must make study data accessible to the monitor, sponsors, or other authorized representatives of the sponsors and regulatory agency inspectors. A file for each subject must be maintained that includes the signed informed consent form and copies of all source documentation related to that subject. The investigator must ensure the availability of source documents from which the information on the CRF is derived.

### **9.3 Source Data Verification and On-Site Audits**

Regulatory authorities, the IEC/IRB, and/or the sponsor's clinical quality assurance group may request access to all source documents, case report forms, and other study documentation for on-site audit or inspection. Direct access to these documents must be guaranteed by the investigator, who must provide support at all times for these activities.

